### Escalation Process

The trial begins with a low dose, enrolling 3-6 subjects in each dose group. The decision to proceed to the next dose group will be based on whether at least 3 evaluable subjects from the previous dose group experience Dose Limiting Toxicity (DLT) and the corresponding safety data within 25 days after the first administration. An evaluable subject is defined as one who has received ≥80% of the planned dose or has experienced DLT after at least one dose

The specific regulations for dose escalation are as follows:

Table 8 Dose Escalation Rules

| **Occurrence of DLT** | **Actions** |
| --- | --- |
| No DLT observed | Proceed to the next dose group |
| 1 DLT observed among 3 subjects | Recruit an additional 3 subjects to receive the same dose of the investigational drug and observe for DLT |
| 1 DLT observed among 6 subjects | Proceed to the next dose group |
| ≥2 DLTs observed among 3 or 6 subjects | Reduce to the previous dose group.   - If there are fewer than 6 evaluable subjects in the previous dose group, recruit an additional 3 subjects to reach a total of 6 evaluable subjects. If no more than 1 DLT is observed among the 6 evaluable subjects, terminate the trial, and that dose group will be considered the MTD. - If there are already 6 evaluable subjects in the previous dose group, terminate the trial, and that dose will be considered the MTD. |

**Enrollment Sequence for Subjects in the Same Dose Group:** At the beginning of each dose group, only 1 subject will be enrolled to observe the tolerability and safety of that subject within 25 days after the first administration.

- Only if this subject does not experience DLT can the remaining 2 subjects in the same dose group be enrolled simultaneously.
- If this subject experiences DLT, enrollment of the third subject can only occur after the second subject has completed the 25-day observation period following the first administration, and only if the second subject has not experienced DLT.

### Individual Dose Adjustment

**1）Dose Escalation**

Dose escalation is not permitted during the single-dose and multiple-dose phases.

In the continuation dosing phase, individual dose escalation for a subject is allowed under the following conditions:

- The subject has received at least 2 cycles of the specified dose of the drug and has tolerated it well, with no dose-limiting toxicities (DLTs) observed;
- For the proposed escalated dose, there are safety data available for at least 2 evaluable subjects 25 days after their first dose, with no DLTs observed;

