| **Research design** | The trial is divided into three phases: (1) Single-Dose Phase: Eligible subjects will be admitted to the ward the night before the trial. On the following morning around 8:00 AM, they will receive an intravenous infusion of Purinostat Mesylate, completed within 30 minutes. After administration, subjects will be monitored for 6 days, with pharmacokinetic blood samples collected at predefined time points. (2) Multiple-Dose Phase (D8-D25): Subjects who complete the single-dose phase may enter the multiple-dose phase. During this phase, doses will be administered on D8, D11, and D15. Subjects will be monitored for the occurrence of dose-limiting toxicity (DLT) and to determine the maximum tolerated dose (MTD). Pharmacokinetic and pharmacodynamic blood samples will also be collected at predefined time points. Completion of the multiple-dose phase will constitute the primary treatment portion of the trial. (3) Extended Treatment Phase: After completing the multiple-dose phase, if subjects tolerate the treatment well and do not experience disease progression, and if the investigator determines that continued treatment could be beneficial, subjects may continue treatment. This will follow a cycle of 21 days, with treatments on D1, D4, D8, and D11 of each cycle. During the extension treatment phase, after completing each administration cycle, subjects will be evaluated by the investigator. If they are well-tolerated without disease progression, and based on the tolerability and pharmacokinetic results from other subjects who have completed treatment in higher dose groups without DLTs, they may escalate to a higher dose group to treat until disease progression or intolerable toxicity occurs. |
| **Research population** | Patients with relapsed or refractory hematologic malignancies, predominantly of B-cell origin, including but not limited to patients with B-cell lymphoma, multiple myeloma, B-cell acute leukemia, T-cell lymphoma, T-cell acute leukemia, whose disease has progressed, relapsed after treatment with standard regimens, or is unsuitable for standard regimens. |

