| **Drug Administration Plan** | The dosing phase of this study includes three stages: the single-dose phase, the multiple-dose phase, and the extended dosing phase. The pharmacokinetics of the single-dose and multiple-dose administrations are combined, during which safety, tolerability, and preliminary efficacy are observed.  **1. Single-Dose Phase**  The single-dose escalation phase will begin with the starting dose and proceed in an ascending order from low to high doses, with 3 to 6 subjects enrolled in each dose group. In each dose group, 3 subjects will be enrolled sequentially, and a single dose will be administered on Day 1 (D1) at that dose, followed by a 6-day observation period (D2-D7). Each subject will receive treatment with a single dose.  **2. Multiple-Dose Phase**  After completing the pharmacokinetic blood sampling for the single-dose administration, if the subject is well-tolerated, they will enter the multiple-dose phase, with doses administered on Days 8, 11, and 15. Each subject will receive the same dose as in the single-dose phase, with the dose-limiting toxicity (DLT) observation period defined as the first administration to 25 days after the first dose. Initially, only one subject will be enrolled in each dose group to observe their tolerability and safety within the 25 days following the first dose. Only if this subject does not experience a DLT will the remaining two subjects in the same dose group be allowed to enroll simultaneously.  If none of the 3 subjects in a dose group experience DLT, the trial will proceed to the next dose group. If 1 out of the 3 subjects in a dose group experiences DLT, an additional 3 subjects will be recruited to receive the same dose of the investigational drug, and they will be monitored for DLT occurrence.  If 1 DLT occurs among the 6 subjects, the trial will proceed to the next dose group. If 2 or more DLTs occur among the 3 subjects, or if 2 or more DLTs occur among the 6 subjects, the trial will be reduced to the previous dose group. If the previous dose group has fewer than 6 evaluable subjects, an additional 3 subjects will be enrolled to bring the total number of evaluable subjects to 6. If no more than 1 DLT occurs among the 6 evaluable subjects, the trial will be halted, and that dose group will be declared as the maximum tolerated dose (MTD). If the previous dose group has already reached 6 evaluable subjects, the trial will be halted, and that dose will be declared as the MTD.  During the multiple-dose escalation trial, real-time analysis of the pharmacokinetic (PK) data for the selected dose groups will be conducted to determine whether the drug reaches a saturation state in the body based on PK and pharmacodynamic (PD) indicators.  **3. Extended Treatment Phase**  After completing the single-dose and multiple-dose phases, if the efficacy assessment indicates clinical benefit for the subject, they will enter the extended dosing phase. In the extended dosing phase, treatment may continue according to the original dosing regimen or with adjustments to the dose based on the subject's tolerability and existing clinical results. Each dosing cycle lasts 21 days, with doses administered on Days 1, 4, 8, and 11 of each cycle. The number of extended dosing cycles will vary based on the patient's efficacy; subjects who achieve an objective response rate of partial response (PR) or higher after 6 cycles may continue receiving the treatment until disease progression, while those who do not reach PR will discontinue the treatment. Efficacy and safety data will continue to be collected during the extended dosing phase. |

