# Study Design

## Overall Description of the Study

This study is a single-center, open-label, dose-escalation Phase I clinical trial that employs a conventional "3+3" dose escalation scheme. A total of 21 to 42 patients with relapsed or refractory hematological malignancies primarily associated with B-cell tumors will be enrolled (including but not limited to B-cell lymphomas, multiple myeloma, B-cell acute leukemia, T-cell lymphomas, and T-cell acute leukemia, in cases of disease progression, relapse, or those who are unsuitable for standard treatment after receiving standard treatment protocols). After obtaining informed consent, participants will undergo screening within two weeks prior to the first administration to confirm eligibility and to conduct a series of baseline assessments.

The study is divided into three phases: (1) Single Administration Phase (D1-D7): Eligible participants will be admitted to the hospital on the night before the trial (D0) and will receive an intravenous infusion of Purinostat Mesylate at approximately 8:00 AM the following day (D1). The infusion will be completed within 30 minutes, and participants will be monitored for six days post-administration. (2) Multiple Administration Phase (D8-D25): Participants who complete the single administration phase will proceed to the multiple administration phase. In this phase, doses will be administered on D8, D11, and D15. Participants will be monitored for the occurrence of dose-limiting toxicities (DLTs) and to determine the maximum tolerated dose (MTD). Completion of the multiple administration phase will constitute the main portion of the study. (3) Extended Treatment Phase: After completing the multiple administration phase, participants who tolerate the treatment well and do not experience disease progression, as determined by the investigator, may continue treatment according to the original protocol if it is deemed beneficial. During the extended treatment phase, each treatment cycle will be evaluated by the investigator for tolerability and absence of tumor progression. Based on the tolerability and pharmacokinetic results from other participants in the higher dose groups that have been completed, if no DLTs are observed, participants may be adjusted to a higher dose group for continued treatment until disease progression or intolerable toxicity occurs.

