The starting dose will be 1.2 mg/m², and dose escalation will be conducted according to the Modified Fibonacci Scheme, with escalation increments of 100%, 67%, 50%, 40%, 33%, and 33%. Only after completing the single and multiple administration phases of the previous dose group, and based on the tolerability and pharmacokinetic results of that dose group, can a decision be made on whether to proceed to the next dose group, until the maximum tolerated dose (MTD) is established. It is anticipated that the MTD will be determined within seven dose groups, with a maximum sample size projected to be 42 participants.

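### Section 3.2.5 and Section 3.1 of the protocol set different conditions for moving an extension-phase subject to a higher dose: 3.2.5 accepts two DLT-free evaluable subjects and names no PK review, while 3.1 asks for tolerability and PK results from completed, DLT-free groups

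*Protocol*

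**What the plan says.** Three places in the protocol govern a move to a higher dose during the extension phase.

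- **Section 3.2.5 (Individual Dose Adjustment, Dose Escalation)** lists two conditions. On the subject's own exposure: "The subject has received at least 2 cycles of the specified dose of the drug and has tolerated it well", without a DLT. On the proposed dose: "there are safety data available for at least 2 evaluable subjects 25 days after their first dose, with no DLTs observed". PK is not mentioned, nor is completion of the higher group. The section does not refer back to 3.1.
- **Section 3.1 (Overall Description of the Study)** allows the move on this basis: "Based on the tolerability and pharmacokinetic results from other participants in the higher dose groups that have been completed, if no DLTs are observed".
- **The synopsis (Research design)** allows it "based on the tolerability and pharmacokinetic results from other subjects who have completed treatment in higher dose groups without DLTs". Here completion is attached to subjects, not to a group.

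Two further rules give context. Section 3.1 opens a new dose group "Only after completing the single and multiple administration phases of the previous dose group", using that group's tolerability and PK results. Section 3.2.4 rests that decision on whether "at least 3 evaluable subjects from the previous dose group experience Dose Limiting Toxicity (DLT) and the corresponding safety data within 25 days" of first dosing. On the order of enrolment within a group, Section 3.2.4 says: "Only if this subject does not experience DLT can the remaining 2 subjects in the same dose group be enrolled simultaneously". The synopsis (Drug Administration Plan) says: "In each dose group, 3 subjects will be enrolled sequentially", and then repeats the allowance for the last two to start together.

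**The concern.** Section 3.2.5 is where an investigator would look for the rule on individual dose changes, and its list reads as self-standing. Someone following it alone could raise a subject's dose in circumstances that Section 3.1 would not allow, in two ways.

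1. **No PK review.** This applies to every move under 3.2.5, even when the higher group is complete. The review has a purpose here: Section 1.4.3.1 reports that in rats a tenfold dose increase gave a 21.7- to 24.4-fold rise in AUC, although exposure in dogs was linear (Section 1.4.3.2).
2. **A group still under observation.** Two evaluable DLT-free subjects satisfy 3.2.5 while a third subject at that dose is still inside the D1–D25 window. A subject who is tolerating treatment could then be moved to a dose that shows a DLT shortly afterwards.

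Because this rule decides who may receive which dose, it has to be settled in the protocol; an analysis plan cannot repair it.

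**Working it through.** **Smallest completed group.** Section 4.1 plans 7 dose groups and 21–42 participants. With 3–6 subjects per group, 7 × 3 = 21 and 7 × 6 = 42, so the stated figure reproduces. The smallest group has 3 subjects, and Section 3.2.4 needs at least 3 evaluable. Two evaluable subjects therefore cannot be a completed group.

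**The conditions side by side.**

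| | Section 3.2.5 | Section 3.1 | Synopsis |
|---|---|---|---|
| Data at the higher dose | at least 2 evaluable subjects, 25 days | completed groups | subjects who completed treatment |
| DLTs at the higher dose | none | none | none |
| PK results | not named | required | required |
| Subject's own exposure | at least 2 cycles | reviewed each cycle | reviewed each cycle |

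The first and third rows conflict between 3.2.5 and 3.1. Between 3.2.5 and the synopsis, the conflict is mainly the third row. The last row is compatible: a review after every cycle can coexist with a two-cycle minimum.

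**When a group can stand at 0 of 2 with a third subject pending.** If the first subject at the dose has a DLT, the no-DLT condition already blocks the move. If the first subject is clear and the next two start together, they finish together and no such state arises from enrolment order. It needs a staggered start, which Section 3.2.4 permits because a simultaneous start is allowed but not required, or a replacement under Section 4.7.

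**Whether the two-cycle minimum closes the gap.** The first subject at the new dose is observed alone for 25 days and the second for 25 more, so 0 of 2 is reached no earlier than 25 + 25 = 50 days after the group opens. Two extension cycles take 2 × 21 = 42 days. The group below has finished its D25 windows before the new group opens, so an undelayed subject from it has passed 42 extension days by then. The minimum does not close the gap.

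**Consequence if a move is made in that state.** The protocol gives no true DLT rate p, so 20%, 33% and 50% are assumed.

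| Quantity | Formula | p = 0.20 | p = 0.33 | p = 0.50 |
|---|---|---|---|---|
| First two DLT-free | (1−p)² | 0.640 | 0.449 | 0.250 |
| All three DLT-free | (1−p)³ | 0.512 | 0.301 | 0.125 |
| First two clear, third has a DLT | p(1−p)² | 0.128 | 0.148 | 0.125 |
| Group later fails Table 8, given 0 of 2 | p[1−(1−p)³] | 0.098 | 0.231 | 0.438 |
| 0 of 2 and later failure, jointly | (1−p)² × p[1−(1−p)³] | 0.062 | 0.104 | 0.109 |

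The fourth row follows Table 8: the third subject has a DLT (p), three more are enrolled, and at least one of those has a DLT, 1−(1−p)³.

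The exact one-sided 95% upper bound on the DLT rate after no events in n subjects is 1 − 0.05^(1/n): 77.6% for n = 2 and 63.2% for n = 3.

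**The case against.** The best defence is that the sections are cumulative. Section 3.2.5 does not say that its list replaces 3.1, and silence on PK does not waive a PK condition stated elsewhere; an investigator who follows the whole protocol meets both. This has some force for PK. It does not rescue the count: if a completed group is always needed, a minimum of two evaluable subjects never has any effect. One can answer that completion in 3.1 was meant to attach to participants, as in the synopsis, so that 3.2.5 simply supplies the number. That is possible, but it is not what 3.1 says. What stands is that the group-completion half of the point rests on 3.1 alone.

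A reader might also infer more than the documents support:

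- **That two subjects falls short of the protocol's own standard for exposing someone to a dose.** The three-subject rule in 3.2.4 governs opening the next dose. At the same dose, 3.2.4 lets two new subjects start after one DLT-free subject, and Table 8 treats three more after 1 DLT in 3. By that comparison, two DLT-free subjects plus two tolerated cycles is not lax. The three-subject rule matters here only because it fixes the smallest completed group.
- **That the sequential enrolment described in the synopsis makes a pending third subject routine.** The same synopsis row then allows the last two subjects to start together.
- **That the percentages measure risk in this trial.** They use assumed rates and apply only if a move is made while a third subject is pending.
- **That dose finding is compromised.** Section 3.2.5 bars individual escalation in the single- and multiple-dose phases, which make up the whole DLT window.

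**Conclusion.** The conflict between Sections 3.2.5 and 3.1 is in the current text and should be resolved. Its importance is minor to moderate. The PK omission reaches every move made under 3.2.5. The possibility of moving someone to a dose whose group is still pending is real but narrow. In that situation, at assumed true DLT rates of 20%, 33% and 50%, the group would go on to fail Table 8 with probability 10%, 23% and 44%. The protocol gives no accrual rate, so the frequency of the situation cannot be computed. Moves are optional, and DLT counts and the MTD decision are unaffected. What is at stake is the safety of individual extension-phase subjects and consistent dosing decisions under a single protocol.

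**What to change.** Replace the second condition in Section 3.2.5 with: *the dose group at the proposed dose has completed its D1–D25 DLT window (at least 3 evaluable subjects, as in Section 3.2.4) with no DLTs, and its tolerability and PK results have been reviewed, as required by Section 3.1.* Align the synopsis so that it, too, refers to the completed group.

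This keeps the no-DLT condition common to all three places, so a group at 1 DLT in 6 would not qualify even though Table 8 lets escalation proceed. The three-subject count is brought in from 3.2.4 to define a completed group; neither 3.1 nor the synopsis states it for individual moves.

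The cost is two wording changes and a short delay before some optional moves. Section 3.1 already calls for each group's PK results before the next group opens, so no new sampling is needed. Repeating the two-cycle minimum in the synopsis and Section 3.1 would be optional editing.

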**2）Dose Reduction and Treatment Interruption**

If a subject experiences a dose-limiting toxicity (DLT) during the single-dose or multiple-dose phases, treatment must be interrupted until the toxicity recovers to Grade 1 or below. Based on the investigator's judgment that the subject may benefit from continued treatment, the subject may resume medication.

In the continuation dosing phase, the dose may be adjusted or treatment may be interrupted according to the following rules:

| **Toxicity** | **CTCAE Grade** | **Measures** |
| --- | --- | --- |
| Nausea and vomiting | Grade 3-4 | If it occurs for the first time, consider using antiemetics for treatment and interrupt the medication until the toxicity recovers to Grade 1 or below. Continue treatment with the original dose, and it is recommended to use antiemetics as a preventive measure.  If it occurs again, interrupt the medication until recovery to Grade 1 or below, and reduce the dose to the previous level. |
| Diarrhea | Grade 3 | If it occurs for the first time, consider using antidiarrheal medication for treatment and interrupt the medication until the toxicity recovers to Grade 1 or below. Continue treatment with the original dose, and it is recommended to use antidiarrheal medication as a preventive measure.  If it occurs again, interrupt the medication until recovery to Grade 1 or below, and when resuming treatment, reduce the dose to the previous level. |
|  | Grade 4 | If it occurs for the first time, consider using antidiarrheal medication for treatment and interrupt the medication until the toxicity recovers to Grade 1 or below. Adjust the dose to the previous level for treatment, and it is recommended to use antidiarrheal medication as a preventive measure.  If it occurs again, discontinue treatment and withdraw from the study. |
| Neutropenia | Grade 3 | ANC: 0.75 - 1.0 × 10^9^ /L, maintain the current dose and continue treatment. ANC: 0.5 - 0.75 × 10^9^ /L, interrupt treatment until ANC recovers to 1.0 × 10^9^ /L, then continue treatment at the original dose. |
| Febrile neutropenia | Grade 3 | Interrupt treatment until ANC recovers to 1.0 × 10^9 /L; when resuming treatment, reduce the dose to the previous level. |
| Thrombocytopenia | Grade 3 | Maintain the current dose of treatment and monitor platelet counts weekly |
|  | Grade 3-4 | Grade 3 thrombocytopenia with bleeding: interrupt treatment until PLT recovers to 50 × 10^9^ /L; when resuming treatment, reduce the dose to the previous level and monitor platelet counts weekly.  Grade 4 thrombocytopenia: interrupt treatment until PLT recovers to 50 × 10^9^ /L; when resuming treatment, reduce the dose to the previous level and monitor platelet counts weekly. |
| Anemia | Grade 3 | Interrupt treatment until Hb recovers to 10 g/dL; when resuming treatment, reduce the dose to the previous level. |
| QTc interval prolongation | Grade 2 | If it occurs for the first time: interrupt treatment until QTc < 450 ms; when resuming treatment, reduce the dose to the previous level.  If it occurs again: discontinue treatment and withdraw from the study. |
| Neurotoxicity | Grade 2 | If it occurs for the first time: interrupt treatment until the toxicity recovers to Grade 1 or below; when resuming treatment, reduce the dose to the previous level.  If it occurs again: discontinue treatment and withdraw from the study. |
| Liver function (elevated ALT and AST levels) | Grade 2 | Baseline normal, with Grade 2 elevation of ALT or AST occurring after treatment.  If it occurs for the first time: interrupt medication until toxicity recovers to Grade 1 or below; when resuming medication, reduce the dose by one level and increase the frequency of liver function monitoring.  If it occurs again: discontinue treatment and withdraw from the study. |
|  | Grade 3 | For patients with normal baseline, if Grade 3 toxicity occurs with ALT or AST > 8 × ULN, discontinue treatment and withdraw from the study.  For patients with Grade 1 baseline, if Grade 3 toxicity occurs with ALT or AST > 8 × ULN, consider discontinuing treatment and withdrawing from the study.  For patients with normal baseline or Grade 1 baseline, if Grade 3 toxicity occurs for the first time with 5 × ULN < ALT or AST < 8 × ULN, interrupt medication until toxicity recovers to Grade 1 or below; when resuming medication, reduce the dose by one level and increase the frequency of liver function monitoring. If it occurs again, discontinue treatment and withdraw from the study. |
|  | Grade 4 | Discontinue treatment and withdraw from the study. |
| Others | Grade 2-3 | For relapsedGrade 2-3 toxicities, except for alopecia and fatigue, treatment must be interrupted until the toxicity recovers to Grade 1 or below; when resuming treatment, reduce the dose to the previous level. |

